## Abstract

**Background:**

Presently available medications and surgical treatments for Parkinson’s disease have limited effects on fine motor problems and often leave patients with significant fine motor disability. Standard of care occupational therapy (OT) yields low efficacy, potentially due to a lack of standard protocols. Neurologic music therapy (NMT) techniques, especially rhythmic auditory stimulation which relies on interaction between rhythm and movement, have shown to be effective in PD gait rehabilitation possibly through their reliance on neural pathways that are not affected by PD. Therapeutic instrumental music performance (TIMP) is one other NMT technique that holds promise but which mode of action and efficacy has not been investigated in PD yet.

**Methods:**

One hundred PD participants will be randomly assigned to receive 15 sessions of either TIMP with rhythm or TIMP without rhythm, standard of care OT, or to be waitlisted (control) over 5 consecutive weeks. Brain oscillatory responses will be collected using magnetoencephalography during an auditory-motor task to understand the underlying mechanisms. The Grooved Pegboard, the UPDRS III finger tap, and the finger-thumb opposition will be assessed to investigate clinical changes related to fine motor function. This project will also serve to confirm or refute our pilot data findings suggesting NMT relies on compensatory brain networks utilized by the PD brain to bypass the dysfunctional basal ganglia.

**Discussion:**

This study aims to use standardized TIMP and OT research protocols for investigating the neuronal pathways utilized by each intervention and possibly study their efficacy with respect to fine motor rehabilitation via a randomized control trial in the PD population.

**Trial registration:**

ClinicalTrials.gov NCT03049033. Registered on September 29, 2020

**Supplementary Information:**

The online version contains supplementary material available at 10.1186/s13063-021-05560-7.

## Introduction

### {6a} Background and rationale

Parkinson’s disease [1] is the second most common neurodegenerative illness and affects 1% of people over age 50 and more than 10 million people worldwide [2]. Notable motor symptoms that manifest from PD are bradykinesia, rigidity, tremors, unnatural gait, and postural instability characterized by impairments in balance and coordination [3]. Besides gross motor symptoms, fine motor impairments in PD cause difficulties with everyday tasks such as writing, self-care, and fine object manipulation [4]. These activity limitations can lead to disability, social isolation, and a reduced quality of life [5]. Presently available medications and surgical treatments for PD have limited effects on fine motor problems, possibly because these symptoms are due to intrinsic dysfunction of the somatosensory cortex [6]. Advances in our understanding of the underlying neurophysiology have helped treat gross motor symptoms. Better evidence-based treatment strategies for PD-related fine motor dysfunction are clearly needed.

In a series of breakthrough studies, [name] and colleagues developed a series of evidence-based interventions collectively identified as neurologic music therapy (NMT), which includes techniques for gross motor neurorehabilitation that rely on interaction between rhythm and movement. Rhythmic auditory stimulation (RAS), one of these NMT techniques, has proven evidence of efficacy for gait rehabilitation in PD [7] and in stroke patients (now included in US VA and DoD as well as Canadian governmental guidelines). The pathological basal ganglia (BG) in PD brains leads to a reduced supply of internally generated movements. In contrast, externally cued movements (i.e., via a beat or a rhythm) during RAS sessions are instantaneously entrained to the period of a rhythmic stimulus possibly bypassing defective pallidocortical projections [8] via the lateral premotor cortex which receives sensory information in the context of externally guided movements [9]. The mechanism of action is called “rhythmic entrainment” where one system's motion or signal frequency entrains the frequency of another system. While published data suggest that RAS facilitates locomotor function in patients with PD [10, 11], effects of NMT techniques on fine motor function have not been investigated yet. Therapeutic instrumental music performance (TIMP) is another NMT technique which uses musical instruments in a therapeutic form to exercise and stimulate functional movement patterns [12]. In stroke patients, a TIMP-like intervention, called music-supported therapy, has shown motor benefits through movement exercises facilitated by musical instruments [13]. No evidence of TIMP-related rehabilitation in PD has been shown yet nor any evidence of how TIMP affects humans’ neurophysiology. Given the increasing interest related to music as a potential therapy for brain diseases, as well as new funding initiatives from the National Institute of Health, furthering our understanding via mechanistic clinical studies seems to hold enormous potential. Occupational therapy (OT) is the standard of care option when pharmacological interventions do not address fine motor impairments for PD patients. OT interventions typically include range of motion and strengthening of the extrinsic and intrinsic muscles, variable hand manipulation tasks, and coordination drills focusing on mass practice of designated movements. Unfortunately, these have a low impact, mainly due to patients’ compliance and lack of standardization.

It is known that neurons in the brain communicate with each other by firing at certain frequencies. Prior studies suggest impaired oscillatory activity in PD, such as excessive beta (15–30 Hz) synchrony [14] and impaired gamma activity [15]. Attempts to normalize beta synchrony in PD such as with deep brain stimulation surgery or dopaminergic medications are associated with improved motor symptoms [16], suggesting an interrelationship between altered brain rhythms and motor dysfunction in PD. In healthy controls, beta and gamma rhythms are suspected to play a role during rhythmic entrainment via a complex network system involving cortical and subcortical areas, such as the supplementary motor area, the parietal cortex and the basal ganglia [17, 18]. The cortical pathways involved in rhythmic entrainment of motor oscillations via NMT techniques are still unknown, and whether the PD brain mobilizes different networks during this process is still under investigation. The main hypothesis of this proposal is that cortical activity associated with fine motor control is impaired in PD and that NMT holds promise to normalize oscillatory activity via compensatory networks between the auditory and motor cortex. Bypassing the dysfunctional basal ganglia, NMT works to improve motor skills through neural entrainment. Regardless of the rehabilitative method used, this will also be the first study looking at the impact of fine motor training on neurophysiology.

### {6b & 7} Research objectives and comparators

The central goal for this study is to investigate the underlying networks used during TIMP and test the rehabilitative power of TIMP techniques for fine motor control in PD. Specifically, the study aims to demonstrate whether the use of musical instruments to specifically promote fine motor function allows differential mobilization of neuronal networks when they are combined with external rhythmic cueing. To allow for an accurate clinical comparator, a standardized OT research protocol will be tested as well.

## Methods

### {9} Study setting

Pre- and post-intervention testing will occur in the magnetoencephalography (MEG) area of the CU Neuromagnetic Lab within the Fitzsimons Building at the University of Colorado Anschutz Medical Campus. TIMP without external rhythm (TIMP-NR) and TIMP with external rhythm (TIMP-RHY) sessions will occur at the neurologic music therapists’ clinic whereas OT sessions will occur at an OT clinic. This study includes locations throughout Colorado for each of these therapy interventions.

### {15, 24 &26a} Recruitment and informed consent

Participants will be recruited from the Movement Disorders Center at University of Colorado Anschutz Medical Campus, from the community via advertisements, fliers, and through support group outreach. After a preliminary telephone screening, evaluation and consent will be obtained at a face-to-face interview between the subject and a member of the research team. Study details will be explained to the subject in a quiet room, without disturbance. Each subject will be asked to review the consent document, approved by the Colorado Multiple Institutional Review Board, and the University of Colorado Committee for the Protection of Human Subjects, which will include HIPAA authorization. Although this trial has minimal risk, subject harms fall under responsibility of the subject and their insurance, as indicated in the consent form.

### {26b} Additional consent provisions for collection and use of participant data and biological specimens

N/A

### {10} Eligibility criteria

Our inclusion criteria for the study include the following: (1) PD patients diagnosed using UK Brain Bank Criteria, (2) ages 45–85 at study entry, (3) provide independent consent, and (4) subjects with stable medications for at least 30 days will be included. Our exclusion criteria consist of the following: (1) features suggestive of other causes of parkinsonism, including cerebrovascular disease or history of major head trauma, (2) inability to move their fingers or hands, [19] Hoehn and Yahr stage 4 or higher, (4) ferrous metal implants which may interfere with the MEG data acquisition, (5) dementia according to the Mattis Dementia Rating Scale—Version 2 [20]. Cutoff score of ≤ 123 on the MDRS is proven to discriminate PD with from without dementia [21], (6) participants engaged in other research studies involving music, and (7) participants whose insurance does not cover OT costs or who have no insurance.

### {8 & 13} Trial design and timeline

After enrollment and screening assessment, 100 PD subjects will be randomly assigned (parallel assignment) in a 1:1:1:1 ratio to TIMP-RHY (25 people), or OT (25 people), or TIMP-NR (25 people) groups, or to wait for 5 weeks (Waitlist control group; 25 people). All PD subjects will undergo a magnetoencephalography (MEG) scan and a battery of tests before and after the TIMP-NR, TIMP-RHY, OT intervention, or twice separated by a 5-week period free of intervention (waitlist control group). First, to capture neural network and neurophysiological changes, participants will perform an MEG scan which engages them in an auditory-motor task. Then, clinical measures will be based on standardized PD neurologic assessments via the Unified Parkinson’s Disease Rating Scale [1], and fine motor assessments will include the Grooved Pegboard Test and finger-thumb opposition tests. Last, to capture changes in quality of life (QOL), we have included the 39-Item Parkinson's Disease Questionnaire (PDQ-39) [22]. The total duration of participation is 5–7 weeks (see the study flowchart in Fig. 1).

**Fig. 1 Fig1:**
[figure not shown]
Study flowchart

### {16a-c} Randomization and assignment of interventions

Group randomization is determined using a Microsoft Excel-based random number generated sequence which relates to one of four possible groups the subject can be randomized into. Subjects will be informed of the 4 possible group assignments. After initial screening, potential participants will be entered sequentially into the randomization list and therefore assigned to the intervention associated with their row. For scheduling and logistic purposes, subjects will learn of their group assignment once they are assigned a study ID and have been scheduled for their first research visit, which needs to occur within a week of the first intervention sessions. Subjects will typically be informed at least 2 weeks prior to starting on the study via email or telephone from our study coordinator. There is a second random number generated sequence for re-randomizing those who were initially randomized into the waitlist control group. This list re-randomizes those participants into either TIMP-RHY or TIMP-NR group or OT group after completing their post-waitlist visit. No data collection will occur for this second assignment.

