### {17a-b} Blinding

Treatment assignment is blinded except for the clinical research coordinator, who is responsible for disseminating the group assignment from the randomization list. Treatment allocation is not blinded for the therapist and participant, as the nature of TIMP and OT therapy does not permit blinding. However, since music and occupational therapists will not collect any data, this should minimize bias. In addition, the participants are blinded to the main hypotheses of the study. Last, the PI, outcome assessors, and study statistician are blinded to all study conditions. No unblinding is permitted under any circumstance.

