### {5d, 21, 22, 23 & 25} Oversight and monitoring

This clinical trial, protocol, and consent form are approved by the Colorado Multiple Institutional Review Board, COMIRB # 16-2308. Amendments are submitted to COMIRB for approval. Important protocol modifications will be communicated to the sponsor for approval.

A physician external to the research team ([name]) provides oversight as our data monitoring committee and is conducting a comprehensive review that occurs bi-annually. Any adverse events, regardless of the occurrence’s relationship to the study, will be documented and reported to the PI without indicating the location of the event, in order to maintain PI blinding. The level of severity and prospective actions are determined by the PI. Serious adverse events are released to COMIRB. Per department standards, routine auditing will occur to ensure all measures and standard operating procedures are followed as outlined in the protocol.

Considering the different stages of this trial, our team members are assigned to different tasks: recruitment (2 staff members), scheduling (study coordinator), randomization and statistical analyses (study statistician), consent process (study coordinator), baseline and post-intervention visits (study PI), and data management (outcome assessor).

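### As written, allocation concealment is not protected, and the stated blinding of the statistician is contradicted by the list of duties

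*Protocol article*

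**What the plan says.** All references are to the Protocol article.

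- **Sequence and assignment**, section {16a-c} Randomization and assignment of interventions: "Group randomization is determined using a Microsoft Excel-based random number generated sequence", and after initial screening "potential participants will be entered sequentially into the randomization list and therefore assigned to the intervention associated with their row". The same section has the study coordinator tell participants their group, usually two weeks or more before they start.
- **Who works from the list**, section {17a-b} Blinding: "Treatment assignment is blinded except for the clinical research coordinator, who is responsible for disseminating the group assignment from the randomization list".
- **Who takes consent**, section {5d, 21, 22, 23 & 25} Oversight and monitoring: "consent process (study coordinator" appears among the duties, and scheduling goes to the same role.
- **When randomisation happens**, section {8 & 13} Trial design and timeline: "After enrollment and screening assessment, 100 PD subjects will be randomly assigned", in equal ratio with 25 per group.
- **The statistician**, section {17a-b}: "the PI, outcome assessors, and study statistician are blinded to all study conditions". The Oversight and monitoring section, however, lists "randomization and statistical analyses (study statistician" as the duties of one role.

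**The concern.** Two protections against bias are at issue.

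The first is allocation concealment. If the person who takes consent can see the next row, knowledge of the coming arm can influence who is entered and when. Analysis cannot reliably repair that kind of selection. With 25 per arm, steering even a few patients could shift baseline severity or motivation between groups.

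The second is analyst blinding. The article claims it as a safeguard, but the duties it assigns to the statistician do not fit the claim.

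Both matter more here than in a masked trial, because participants and therapists know the treatment. In addition, participants usually learn their arm well before starting, and only complete pre/post pairs are analysed. Arm-dependent withdrawal before baseline would therefore drop out of the analysis unseen.

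**Working it through.** This point disputes no figure, so no calculation applies. The planned numbers agree with each other (4 × 25 = 100). The check is a comparison of what the sections say about roles and order.

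**1. Who can see the list**

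- Section {16a-c}: the arm is fixed by the next sequential row of an existing list. The sentence is passive and does not name who makes the entry.
- Section {17a-b}: the clinical research coordinator is the exception to blinding and gives out assignments from that list.
- Oversight and monitoring: the study coordinator handles consent and scheduling.

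The titles differ, but section {16a-c} gives the study coordinator, and section {17a-b} the clinical research coordinator, the task of passing on group assignments. Reading them as one role is well supported, though it remains an inference. On that reading, the person taking consent works from the allocation list. No sealed, central or one-at-a-time release is described.

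**2. Whether consent comes before allocation**

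- Section {8 & 13}: randomisation follows enrolment and the screening assessment.
- Section {16a-c}: people still called potential participants are entered after an initial screening.
- Section {15, 24 & 26a} Recruitment and informed consent: a telephone screen comes first, and consent follows at a face-to-face meeting.

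If the initial screening in {16a-c} is the telephone screen, the arm is fixed before consent. If it is the later evaluation, the arm is fixed afterwards. The article does not say which, so allocation before consent is not excluded.

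**3. Whether the statistician can be blinded**

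- Section {17a-b}: the statistician is blinded.
- Oversight and monitoring: the statistician has randomisation and the analysis.

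Both statements can be true only if someone else holds the list, or if the analysis is run on masked arm codes. Neither is stated.

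**4. The two parts together**

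- If the statistician operates the list, the coordinator might receive one assignment at a time. The statistician then knows the allocations, and the blinding claim fails unless the analysis is masked.
- If the coordinator operates the list, the statistician may only have generated it. The person taking consent then has the list in hand. A statistician who kept a copy could also match rows to participants by order of entry.

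Under either division of work, at least one of the two protections is not secured by the text.

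**The case against.** The strongest reply is that an unclear division of roles is not a demonstrated failure. That is fair on several counts.

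- **Foreseeability.** A reader might infer that the coordinator could foresee all 100 allocations. The article does not support this. It says that the coordinator gives out assignments from the list, not that later rows are visible or that the coordinator keeps the list.
- **Separate tasks.** Recruitment is given to two other staff members, and section {15, 24 & 26a} says only that someone on the research team takes consent. The Oversight section is more specific on consent and names the coordinator, so this softens the concern without removing it.
- **Incentive.** Waitlist participants are later re-randomised to one of the three therapies, which weakens the motive to steer patients away from the waitlist.
- **Arm sizes.** A reader might also infer that an Excel sequence will give unequal arms. The article does not say whether the sequence is restricted, and a shuffled list of 25 rows per arm would meet the stated ratio exactly. Arm imbalance would in any case not measure concealment or analyst blinding.
- **Condensed article.** A fuller protocol may describe a concealment step or masked coding.

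The conflict between what is actually printed still stands. The statistician is called blinded in one section and given randomisation in another, and allocation is placed after enrolment in one section and after initial screening in another. The roles that are stated put consent and the allocation list with what reads as the same coordinator.

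**Conclusion.** The point holds in this form: concealment is not protected as written, and the analyst-blinding statement is contradicted by the duties assigned. The documents do not support saying that concealment was broken or that the analysis will in fact be unblinded.

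The size of any bias cannot be calculated from the article. The exposure is the allocation process for the 100 planned participants and the analysis of their data. Recruitment began in February 2019, so some allocations may already be beyond protection. The article does not say how many.

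The concealment part assumes that the two coordinator titles are one role. The timing part rests on the undefined initial screening. The statistician part needs no assumption beyond reading the two sections together. It would be resolved if the list were held elsewhere or the analysis used masked codes, and if the article said so.

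**What to change.** 1. **Remaining participants.** Release each assignment singly, and only once consent and eligibility are recorded, from a list that the person taking consent cannot see. The REDCap system already used for data entry could do this if its set-up allows; the article mentions it only as a database. Otherwise an existing team member not involved in consent can hold the list.
2. **Analysis.** Have the statistician work with arms coded A to D until the primary analyses are locked. An existing team member who does not analyse the data should hold the key. If the statistician has already seen the list, correct the statement in section {17a-b} instead of leaving it in place.
3. **Text.** Reconcile sections {8 & 13}, {16a-c}, {17a-b} and {5d, 21, 22, 23 & 25}. They should say who generates the list, who holds it, who releases assignments, and that consent comes before allocation.
4. **Participants already randomised.** Report the process that was actually used.

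The cost is minor set-up work and an amendment. Existing staff can fill the roles, and no visits are added. The change cannot protect allocations already made; for those, reporting is the only remedy.

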### {17a-b} Blinding

Treatment assignment is blinded except for the clinical research coordinator, who is responsible for disseminating the group assignment from the randomization list. Treatment allocation is not blinded for the therapist and participant, as the nature of TIMP and OT therapy does not permit blinding. However, since music and occupational therapists will not collect any data, this should minimize bias. In addition, the participants are blinded to the main hypotheses of the study. Last, the PI, outcome assessors, and study statistician are blinded to all study conditions. No unblinding is permitted under any circumstance.

### {11a-d} Interventions

*(i). TIMP*: Research participants will work with a bachelor’s or master’s level, board-certified MT, neurologic music therapist part of our team 3 times a week for 5 consecutive weeks. Based on the NMT principles, our TIMP interventions utilize a weighted keyboard to allow for auditory feedback of force exerted and will provide an appropriate amount of physical resistance against the finger strike. This offers opportunities for fine motor strength training in addition to working on dexterity. Castanets are being be used as well, for strengthening pincer grasp, a skill that helps turning pages in a book or picking up coins. Last, fine and gross motor warm-ups including range of motion exercises are included in each session.

